### 3.2. Sample Size

To test intervention effects, there is an intended recruitment of 226 participants. Based on previous research in this field and ongoing research within this population group [56], it is anticipated that there will be approximately a 25% attrition over the four weeks of follow-up for reasons such as changes in job status, vacancy, and failure to complete questionnaires. A total sample of approximately 180 completing participants (90/group) is required to detect a medium effect in habit development towards physical movement. This sample was calculated by a power analysis using WebPower program [57]. Significance level (alpha) was established at 0.05 to avoid a Type 1 error and effect size was determined at f = 0.35. This means that for a 95% chance of detecting a significant intervention effect at a four-week follow-up, approximately 90 participants are needed in each group.

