## 4. Data Analyses

To assess the effect of the intervention on reducing occupational sedentary behavior and increasing occupational physical movement; as well as the interventions effect on increasing occupational physical movement habit and its effects on decreasing occupational sedentary behavior habit, four mixed methods 2 (condition/group) × 3 (time) ANOVA’s will be conducted. To assess the overall effects of the intervention, group (control or intervention) will be used as the between-subjects independent variable; time (baseline/T1, T2 and T3) will be used as the within-subjects independent variable with occupational sedentary behavior, occupational physical movement, occupational physical movement habit, and occupational sedentary behavior habit as the dependent variables. Each ANOVA will use an adjusted alpha level of 0.0125 to protect from inflation of type I error. Results, however, will report on any effects using the conventionally accepted significance cut-off level of 0.05 as well as the pre-specified cut-off level of 0.0125. Where an ANOVA indicates a significant time*group interaction for either of the dependent variables, a simple effects analysis will be conducted.

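### The stated 95% power is calculated at alpha 0.05, but the planned tests use alpha 0.0125, so it is not the power of those tests

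*Protocol article*

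**What the plan says.** Section 3.2 of the protocol article gives the basis of the sample size. The target effect is on one outcome: "A total sample of approximately 180 completing participants (90/group) is required to detect a medium effect in habit development towards physical movement". On the inputs it says "Significance level (alpha) was established at 0.05 to avoid a Type 1 error and effect size was determined at f = 0.35", and the conclusion is "for a 95% chance of detecting a significant intervention effect at a four-week follow-up, approximately 90 participants are needed in each group". WebPower is named as the program. The type of effect (between-group, within-subject or interaction) and the nonsphericity coefficient are not given.

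Section 4 sets out the analysis: "four mixed methods 2 (condition/group) × 3 (time) ANOVA’s will be conducted", one each for occupational sedentary behavior, occupational physical movement, physical movement habit and sedentary behavior habit. On the test level it says "Each ANOVA will use an adjusted alpha level of 0.0125 to protect from inflation of type I error". It adds: "Results, however, will report on any effects using the conventionally accepted significance cut-off level of 0.05 as well as the pre-specified cut-off level of 0.0125".

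Neither section gives a power or a sample size at 0.0125.

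**The concern.** The two sections use different significance levels for the same test. Movement habit is the outcome that Section 3.2 sizes for, and it is also one of the four outcomes that Section 4 tests at 0.0125. With everything else equal, a stricter level lowers power, so a figure calculated at 0.05 cannot be carried over unchanged.

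This matters when the result is read. A movement-habit result with a p-value between 0.0125 and 0.05 would miss the pre-specified threshold, and readers would judge that miss against a 95% claim made for a different threshold. Section 4 also commits to reporting at 0.05, so the only level with a stated power would be the one that does not protect the family of four tests.

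**Working it through.** **Inputs from the documents.** N = 180 completers (90 per group), f = 0.35, alpha 0.05 and power 95% (Section 3.2); alpha 0.0125 for each of four 2 × 3 ANOVAs (Section 4); 226 recruits and 25% attrition (Section 3.2).

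**Assumptions.** Power comes from the noncentral F distribution with noncentrality λ = f² × N × ε, taken to be the repeated-measures convention of the named program. ε is the nonsphericity coefficient (1 = no correction).
- 2-df group-by-time interaction: df1 = 2ε, df2 = 2(N − 2)ε.
- 1-df group effect: df1 = 1, df2 = N − 2, ε = 1.

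**Step 1. Try to reproduce the plan's figure (alpha 0.05, f = 0.35, N = 180).** With ε = 1, λ = 0.1225 × 180 = 22.05.

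| Effect | Power at N = 180 | N for 95% |
|---|---|---|
| Interaction, 2 df | 99.1% | 128 |
| Group, 1 df | 99.7% | 109 |

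The pair (180, 95%) does not follow from the printed inputs alone. It is reached only by adding or changing an input: ε about 0.63 with f = 0.35 for the interaction; f about 0.294 for the interaction with ε = 1; or f about 0.270 for the group effect.

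**Step 2. Move to alpha 0.0125, taking f = 0.35 literally (N = 180, λ = 22.05).**
- Interaction: df 2 and 356, critical F 4.44, power 96.7%. 95% needs 166 completers.
- Group effect: df 1 and 178, critical F 6.37, power 98.4%. 95% needs 144 completers.

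**Step 3. Move to alpha 0.0125, taking the protocol's 95% at 0.05 with N = 180 as correct.**

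| Calibration | λ at N = 180 | Power at 0.0125 | N for 95% at 0.0125 |
|---|---|---|---|
| Group effect, f = 0.270 | 13.14 | 86.3% | 239 |
| Interaction, f = 0.294, ε = 1 | 15.57 | 86.7% | 233 |
| Interaction, f = 0.35, ε = 0.63 | 13.89 | 86.5% | 237 |

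These rows are not three independent confirmations. Each was tuned to give 95% at 0.05, so close agreement at 0.0125 is to be expected.

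**Step 4. Between the two readings (interaction, f = 0.35, N = 180, alpha 0.0125).** ε = 0.9 gives 95.1%, ε = 0.8 gives 92.8% and ε = 0.7 gives 89.5%.

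**Step 5. Keep attrition apart.** Section 3.2's own recruitment and attrition leave 226 × 0.75 = 169.5 completers, not 180. At 0.0125 that number gives 95.6% (interaction) or 97.8% (group effect) on the literal reading, and 83.8-84.0% on the Step 3 calibrations. The drop from 180 to 169.5 is a separate matter from the alpha mismatch.

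**Step 6. Why 0.05 cannot simply be used for all four tests.** If the four tests were independent, the familywise error would be 1 − 0.95⁴ = 18.5% at 0.05, against 1 − 0.9875⁴ = 4.9% at 0.0125.

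**The case against.** The strongest reply is that the printed inputs, f = 0.35 and 180 completers, give more than 95% power at 0.0125 under the simplest models. The arithmetic is right, and it rules out any flat statement that power is lost. It does not rescue Section 3.2, because on that reading 180 completers give 99.1-99.7% at 0.05 and the printed 95% is wrong for another reason.

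A second reply is that 180 may in fact have been calculated at 0.0125: with f = 0.35 and ε = 0.9 it gives 95.1% there. That is possible, but then the alpha printed in Section 3.2 is wrong, and the sentence needs the same correction.

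A third reply is that 0.05 is coherent for a single primary outcome. Appendix B lists only habit as primary, and Section 4 openly reports at 0.05 too. But Section 4 applies 0.0125 to each ANOVA and calls that the pre-specified level, and Section 3.5 also counts limiting sedentary behavior among the primary outcomes. Dual reporting is disclosed in advance; it does not make 0.05 the pre-specified level.

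It is also fair to say that the mismatch changes no estimate, no test and no type I error rate. It affects one stated power figure.

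A reader might infer that the trial is underpowered, or that its type II error roughly triples. The documents support neither. The 86-87% needs a back-solved f or an ε that the article does not contain. Even then, alpha alone takes the type II error from 5% to about 13.5%; about 16% is reached only by adding the attrition shortfall.

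**Conclusion.** The point holds as an inconsistency between Sections 3.2 and 4: the 95% is tied to alpha 0.05, and the planned tests, including the one being sized, use 0.0125. That much needs no assumption.

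The size is conditional. With 180 completers, power at 0.0125 is about 86-87% if the protocol's own 95% at 0.05 is correct, and 96.7% (2-df interaction) or 98.4% (1-df group effect) if f = 0.35 is literal and uncorrected. All these figures rest on the noncentrality convention stated above. The article does not say which effect type or nonsphericity coefficient was used, so it cannot settle where in that range the trial lies. Whether power is adequate at 0.0125 remains open.

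**What to change.** Re-run the calculation and restate Section 3.2 at the alpha that will be used: 0.0125 if the four co-equal tests stay, or 0.05 if a single primary outcome is named and tested at that level, with Section 4 amended to match. State the effect type, the nonsphericity coefficient and the expected number of completers, so that the figure can be reproduced.

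The enrolment target can stay. The resulting power should be reported as it falls, above or below 95%. If it falls below, keeping the target means accepting the lower power, and the text should say so.

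The cost is one re-run of the power analysis and a few revised sentences, with the change recorded in the OSF registration, where Section 2 says deviations will be updated.

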### 3.3. Measurement

Data will be collected online via self-reported pre- and post-intervention questionnaires hosted on Qualtrics software. Baseline (T1) data will be collected upon registration for the intervention, T2 data will be collected two weeks post-baseline, and T3 data will be collected four weeks post-baseline (Figure 1).

### 3.4. Demographic Measures

Demographic data will be collected at baseline and will include age (in years), gender (male, female, non-binary, and prefer not to say), residential postcode, current marital status (married registered, de-facto relationship, widowed, divorced, separated, never married), workplace environment (commercial office, home office, mixture of commercial and home office), occupation, education level, family taxable income range, and ethnicity.

### 3.5. Measured Variables

The primary outcome variables will assess the effectiveness of the intervention on limiting occupational sedentary behavior and developing habits towards occupational physical movement within the workplace. The Occupational Sitting and Physical Activity Questionnaire (OSPAQ) is used to measure occupational sedentary behavior and occupational physical movement. The OSPAQ has been validated for use with both commercial office and home office working populations [58,59,60]. To measure the construct of habit for occupational sedentary behavior and physical movement the four-item Self-Report Behavioral Automaticity Index is used [61]. For occupational physical movement habit, participants will be asked to rate their agreement with the following statements “Do you agree that doing occupational physical movement as part of your daily work routine is something: I do automatically; I do without having to consciously remember; I do without thinking; I start doing before I realize I am doing it”, measured on a 7-point Likert scale (1 = strongly disagree, 7 = strongly agree). To measure habit to engage in occupational sedentary behavior, participants will be asked to rate their agreement with the following statements “ Do you agree that engaging in occupational sedentary behavior as part of your daily work routine is something: I do automatically; I do without having to consciously remember; I do without thinking; I start doing before I realize I am doing it”, measured on a 7-point Likert scale (1 = strongly disagree, 7 = strongly agree). Similar items have been used in previous research [23,49,62].

### 3.6. Study Conditions

#### 3.6.1. Control Group

Participants in the control group are provided with an information sheet adapted from the World Health Organization recommendations on physical activity as well as the Canadian guidelines on sedentary behavior [63]. The World Health Organization recommends adults should aim to do more than 150 min of moderate to vigorous physical activity over the week [13]. Canadian guidelines for sedentary behavior involve limiting sedentary time to eight hours or less and breaking up long periods of sitting as often as possible, along with replacing sedentary behavior with additional physical activity [63]. The information pertains to the risks of increased sedentary behavior and the health benefits of increased movement during the day.

#### 3.6.2. Intervention Group

Along with the information sheet, participants allocated to the intervention group will be provided with a digital poster outlining the positive normative beliefs of other office workers towards movement in the workplace. This poster is developed based on previous literature [49] and guided by literature on the social norms approach [25,64,65,66,67]. Along with this poster, participants are provided with the ‘10 Top Tips’ poster, which includes 10 simple behaviors that can be performed within the workplace to increase movement during the day. Participants are prompted to choose tips that they are confident they could perform and write an action plan outlining where, when, and how they intend to implement their chosen tips, along with a coping plan of how they intend to overcome potential barriers to behavioral production. Following this, participants will be asked to write an encouraging statement to instigate their self-efficacy towards achieving their tips. Furthermore, participants will be provided with a self-monitoring tick sheet that can be used to monitor their behavioral progress. The intervention group is encouraged to print their action and coping plans as reminders of their intentions and to email the self-monitoring tick sheet to the first author at the end of each week.

## 4. Data Analyses

To assess the effect of the intervention on reducing occupational sedentary behavior and increasing occupational physical movement; as well as the interventions effect on increasing occupational physical movement habit and its effects on decreasing occupational sedentary behavior habit, four mixed methods 2 (condition/group) × 3 (time) ANOVA’s will be conducted. To assess the overall effects of the intervention, group (control or intervention) will be used as the between-subjects independent variable; time (baseline/T1, T2 and T3) will be used as the within-subjects independent variable with occupational sedentary behavior, occupational physical movement, occupational physical movement habit, and occupational sedentary behavior habit as the dependent variables. Each ANOVA will use an adjusted alpha level of 0.0125 to protect from inflation of type I error. Results, however, will report on any effects using the conventionally accepted significance cut-off level of 0.05 as well as the pre-specified cut-off level of 0.0125. Where an ANOVA indicates a significant time*group interaction for either of the dependent variables, a simple effects analysis will be conducted.

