The current study aims to develop an online habit-based intervention designed to reduce sedentary behavior within the workplace, using environmental cues to instigate simple behavioral changes. Four hypotheses are preregistered for the current study. Based on previous research, the primary objective is to test the effectiveness of the intervention on limiting occupational sedentary behavior and increasing occupational physical movement habits within the workplace. It is hypothesized that reported occupational sedentary behavior will have a decrease (H1) and reported occupational physical movement will have an increase (H2) across baseline (T1) and follow up points two weeks post baseline (T2) and four weeks post baseline (T3) in comparison to those in the control group. It is further expected that occupational physical movement habit will have an increase (H3) and occupational sedentary behavior habit will have a decrease (H4) across baseline (T1) and follow up points two weeks post baseline (T2) and four weeks post baseline (T3).

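### Testing all four hypotheses at a flat 0.0125 is valid, but Holm's step-down procedure gives the same 5% family-wise error with equal or better power at no cost (minor)

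*Protocol article*

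**What the plan says.** The Introduction states: "Four hypotheses are preregistered for the current study". They are less occupational sitting (H1), more occupational movement (H2), a stronger movement habit (H3) and a weaker sitting habit (H4). Section 4 gives each its own analysis, "four mixed methods 2 (condition/group) × 3 (time") ANOVAs, and sets the threshold: "Each ANOVA will use an adjusted alpha level of 0.0125 to protect from inflation of type I error". The next sentence adds that the results "will report on any effects using the conventionally accepted significance cut-off level of 0.05 as well as" the prespecified 0.0125. No step-down, hierarchical or gatekeeping order is described.

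Section 3.2 gives the design figures used below: "A total sample of approximately 180 completing participants (90/group) is required to detect a medium effect in habit development towards physical movement"; "Significance level (alpha) was established at 0.05 to avoid a Type 1 error and effect size was determined at f = 0.35"; and a sample meant "for a 95% chance of detecting a significant intervention effect at a four-week follow-up".

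**The concern.** The flat rule holds every hypothesis to 0.0125 whatever the other three show. Once one hypothesis has been rejected, at most three true nulls can remain, so the next test can use a larger share of the 5% without raising the family-wise error. The flat rule leaves that share unused.

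What is at stake is power for the second, third and fourth hypotheses. The programme is expected to work through habit, so its full account needs the behaviour and habit outcomes to succeed together. If several effects are real, the flat rule will leave some of them unconfirmed that an equally strict rule would confirm.

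**Working it through.** **1. The plan's threshold.** Four tests and a family-wise level of 0.05 give 0.05/4 = 0.0125, which reproduces exactly. With independent tests the family-wise error is 1 − (1 − 0.0125)^4 = 0.049. The rule is valid.

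**2. Holm's rule.** Order the four p-values and compare them in turn with 0.05/4 = 0.0125, 0.05/3 = 0.0167, 0.05/2 = 0.025 and 0.05. Stop at the first that fails. Any p-value at or below 0.0125 passes at whatever step it is reached, so every flat-rule rejection is also a Holm rejection. The first step is the same under both rules, so the chance of at least one rejection is identical.

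**3. Illustration (invented p-values).** Take 0.004, 0.010, 0.015 and 0.030. The flat rule rejects two. Holm rejects all four: 0.004 ≤ 0.0125, 0.010 ≤ 0.0167, 0.015 ≤ 0.025 and 0.030 ≤ 0.05.

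**4. Model for the size of the gain.** From the protocol: N = 180 completers, two groups, three time points, f = 0.35, 95% power at 0.05. Assumed: sphericity, so the group-by-time test has 2 and 2 × (180 − 2) = 356 df; noncentrality λ = N f²; between-outcome correlation 0 or 0.5, because the protocol gives none.

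Under this model the stated f and the stated power are not the same effect. At f = 0.35, λ = 180 × 0.1225 = 22.05, and power at 0.05 is 99.1%, not 95%. Power of 95% at 0.05 needs λ ≈ 15.57, or f = √(15.57/180) ≈ 0.29. Both readings are shown, with a smaller effect (80% power at 0.05, λ ≈ 9.72, f ≈ 0.23) as a sensitivity case.

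**5. All four effects real** (200,000 simulated trials per case):

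| Effect on each outcome | Correlation | Per outcome, flat → Holm | All four confirmed, flat → Holm |
|---|---|---|---|
| f = 0.35 (λ = 22.05) | 0 | 96.7% → 99.1% | 88% → 96% |
| f = 0.35 (λ = 22.05) | 0.5 | 96.7% → 98.8% | 90% → 97% |
| 95% power at 0.05 (λ = 15.57) | 0 | 86.7% → 94.0% | 56% → 81% |
| 95% power at 0.05 (λ = 15.57) | 0.5 | 86.7% → 92.7% | 67% → 84% |
| 80% power at 0.05 (λ = 9.72) | 0 | 62% → 73% | 15% → 38% |
| 80% power at 0.05 (λ = 9.72) | 0.5 | 62% → 71% | 31% → 52% |

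**6. Fewer real effects.** With two of four real, power per outcome rises by about 1 point at f = 0.35 (96.7% to 97.4%), 2 points in the 95% case (86.7% to 88.6%) and 2.5 points in the 80% case. With one real effect, the change is about 0.1 point or less.

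**7. Error check.** Holm's simulated family-wise error stayed at or below 5% in every configuration with true nulls, including all four null.

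**The case against.** The strongest reply is that nothing here is wrong. The flat 0.0125 is exact, prespecified, simple and valid, and at the protocol's own f = 0.35 it already gives 96.7% power per outcome. That stands, and it is why the point is minor. A reader might infer that the plan fails to control type I error at this threshold; it does not fail.

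Second, no section makes confirming all four hypotheses a condition of success. Section 3.2 sizes the trial on movement habit alone, and Appendix B lists habit development as the primary outcome. This also stands: the large all-four gains describe how complete the confirmed picture would be, not whether the trial succeeds. It would also be an overreading to attach the 56% to 81% figure to f = 0.35; it belongs to the smaller effect implied by 95% power.

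Third, a reader might infer that the loss is greatest because the outcomes are correlated, since one questionnaire "is used to measure occupational sedentary behavior and occupational physical movement". The figures run the other way. In the 95% case, moving from correlation 0 to 0.5 shrinks the per-outcome gain from 94.0 − 86.7 = 7.3 points to 92.7 − 86.7 = 6.0 points, and the all-four gain from about 24 to about 17 points. Holm gains from several effects being real, not from dependence between outcomes.

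Fourth, Section 4 also reports results at 0.05, so a p-value of 0.015 or 0.030 would not be hidden. That is true, but visibility is not confirmation: four independent tests at an unadjusted 0.05 carry a family-wise error of 1 − 0.95^4 = 18.5%. Holm gives such results a valid route to confirmatory status.

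**Conclusion.** The point holds as a minor, free improvement. That Holm is never worse than the flat rule, at the same 5% family-wise error, needs no assumption about effect size or correlation. The size of the gain does depend on assumptions. With all four effects real it is about 2 points per outcome at f = 0.35, and 6 to 7 points if each outcome has 95% power at 0.05. For confirming all four it is about 7 to 9 points on the first reading and 17 to 24 on the second. These figures rest on 180 completers, sphericity, λ = N f², equal effects on all four outcomes and a between-outcome correlation of 0 to 0.5.

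**What to change.** In Section 4, replace the sentence that fixes 0.0125 with: *The four group-by-time p-values will be tested with the Holm step-down procedure at a family-wise alpha of 0.05 (ordered p-values compared in turn with 0.0125, 0.0167, 0.025 and 0.05, stopping at the first non-significant result); Holm-adjusted p-values will be reported.*

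The next sentence must change too, because it still names a single prespecified cut-off of 0.0125 and would contradict the stepped thresholds. It should say that results at an unadjusted 0.05 are descriptive only. Without that label, the 5% family-wise level would not cover the claims made.

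Post a dated update to the OSF registration before any outcome data are analysed; Section 2 already commits to updating it when the plan changes. The timing matters because the change relaxes a registered rule.

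The cost is two sentences and a registry update, with no extra participants or data. The one drawback is that fixed 98.75% confidence intervals, if used, would no longer mirror every test decision; Section 4 plans none.

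### Two significance cut-offs, 0.0125 and 0.05, apply to the same four ANOVAs and the plan does not say which one governs, so family-wise error control is not assured

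*Protocol article*

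**What the plan says.** The Introduction of the protocol article states that "Four hypotheses are preregistered for the current study". Section 4 matches them with one analysis per outcome: "four mixed methods 2 (condition/group) × 3 (time) ANOVA’s will be conducted". The outcomes are occupational sedentary behavior, occupational physical movement, and the habit score for each.

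Section 4 then gives three consecutive rules:

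- The adjusted level: "Each ANOVA will use an adjusted alpha level of 0.0125 to protect from inflation of type I error".
- The second level: results, it says, "will report on any effects using the conventionally accepted significance cut-off level of 0.05 as well as the pre-specified cut-off level of 0.0125".
- The entry condition for follow-up tests, with no level attached: "Where an ANOVA indicates a significant time*group interaction for either of the dependent variables, a simple effects analysis will be conducted".

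Section 3.2 sizes the trial at the unadjusted level: "Significance level (alpha) was established at 0.05 to avoid a Type 1 error and effect size was determined at f = 0.35".

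**The concern.** The first rule gives up some power in exchange for protection over four tests. The second, introduced by a contrasting word, places a looser significance level beside it for the same tests. The third depends on a result being significant without saying at which level. Nothing in Section 4 ranks the two levels or describes the 0.05 results as descriptive or exploratory.

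The rest of the article does not settle the matter. The sample size rests on 0.05. Section 5 describes what a successful intervention would achieve but gives no statistical criterion. No outcome hierarchy helps either: Section 3.5 treats both sedentary behavior and movement habit as primary, whereas Appendix B makes habit primary and reduced sedentary behavior secondary.

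What is at stake is how a p-value between 0.0125 and 0.05 is read. On the present text, one author could call it support for a hypothesis and another could call it a failure, and both could cite Section 4. A related looseness is that the second rule covers effects of any kind. In the Introduction, H1 and H2 are stated relative to control, but H3 and H4 are worded only as change over time. The plan should therefore also say that the group-by-time interaction, and not a time main effect, is the test of all four.

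**Working it through.** **Inputs from the document.** Four ANOVAs (Section 4) for four hypotheses (Introduction); per-ANOVA level 0.0125 and second level 0.05 (Section 4).

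**Assumptions.** One test per ANOVA, the group-by-time interaction; all four null hypotheses true. The correlation between the four test statistics is not given, so a range is shown.

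**Step 1: reproduce the plan's figure.** Bonferroni over four tests: 0.05 / 4 = 0.0125. This matches exactly.

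**Step 2: upper bounds, whatever the correlation.**
- At 0.0125: 4 × 0.0125 = 0.05.
- At 0.05: 4 × 0.05 = 0.20.

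**Step 3: independent tests.** Family-wise error = 1 − (1 − α)^4.
- At 0.0125: 1 − 0.9875^4 = 0.049.
- At 0.05: 1 − 0.95^4 = 0.185.
- Ratio: 0.185 / 0.049 ≈ 3.8.

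**Step 4: correlated tests.** Simulation of four equally correlated two-sided normal tests, 2,000,000 draws for each correlation. This is a normal approximation to the interaction F tests, used for scale only.

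| Assumed correlation | Judged at 0.05 | Judged at 0.0125 |
|---|---|---|
| 0 | 18.5% | 4.9% |
| 0.3 | 17.4% | 4.7% |
| 0.5 | 15.6% | 4.3% |
| 0.7 | 13.1% | 3.7% |
| 0.9 | 9.3% | 2.6% |

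Even at a correlation of 0.9, judging at 0.05 leaves the error rate well above 5%.

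**Step 5: power if 0.0125 governs.** Section 3.2 gives f = 0.35 and 180 completers. Take f as the interaction effect, with noncentrality f² × N × ε, where ε is the nonsphericity correction (not stated in the document). With ε = 1, the noncentrality is 0.35² × 180 = 22.05 on 2 and 356 degrees of freedom, and power at 0.0125 is 0.967. With ε = 0.63, power at 0.0125 is about 0.86, against 0.95 at 0.05.

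**The case against.** The strongest reply is that the plan has already chosen. It assigns 0.0125 to every ANOVA, gives the reason, and calls that level pre-specified, while 0.05 is called only conventional. Both levels are fixed in advance and both are to be shown. A p-value of 0.03 would therefore have to be reported as missing the pre-specified level, and a reader would see that. Reporting against a second level does not by itself alter the error rate of the first.

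Most of this stands, and it rules out some stronger readings:

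- A reader might infer that the plan has no family-wise error control. It does not go that far: a valid Bonferroni level is stated, and control is lost only if conclusions are drawn at 0.05, which the text neither says nor excludes.
- A reader might infer that any effect with p below 0.05 will be declared significant, or counted as support for a hypothesis. The text promises reporting against that cut-off, not a claim.
- A reader might count two main effects and one interaction for each of four outcomes and quote 1 − 0.95^12 = 46%. That treats all 12 tests as confirmatory and independent, which Section 4 does not say; only the interaction leads to follow-up. On the same count, 0.0125 gives 1 − 0.9875^12 = 14%, so that figure concerns the size of the family as well as the 0.05 sentence.

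It might also be said that the preregistration or a separate analysis plan could name the governing level. That is possible, but neither is shown. The difficulty here is not something left out of a condensed article: the second cut-off is in its text, as is a follow-up rule that turns on an undefined use of the word significant.

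**Conclusion.** The point holds as one of an unstated governing rule. Two cut-offs apply to the same four tests, neither is named as the one that decides H1 to H4, and the entry level for simple effects is undefined. Family-wise control at 5% is therefore possible under the plan but not guaranteed by it.

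The size is conditional on 0.05 being used for conclusions: 18.5% with independent tests, falling to about 9% at a correlation of 0.9, against a ceiling of 5% at 0.0125. The correlations are assumptions, and the ceiling counts one interaction test per outcome. The ambiguity touches the rule that fixes the trial's conclusion, so it deserves correction even though the design, outcomes and model are unaffected.

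**What to change.** Replace the 0.05 sentence in Section 4 with a statement along these lines: support for each of H1 to H4, and entry to the simple effects analysis, will be judged only on the group-by-time interaction, at 0.0125 for each of the four outcomes; exact p-values and confidence intervals will be reported for all outcomes. If the authors wish to keep the 0.05 comparison, they should add that results between 0.0125 and 0.05 are descriptive and do not count as support.

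Holm over the four outcomes is an optional alternative. The ordered p-values are compared in turn with 0.05/4 = 0.0125, 0.05/3 = 0.0167, 0.05/2 = 0.025 and 0.05, stopping at the first failure. It keeps family-wise error at 5% and never rejects fewer hypotheses than flat Bonferroni. The present Bonferroni level is valid, so this is a refinement and not a correction.

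The cost is one or two sentences in Section 4 and the same change in the registration, which Section 2 says will be updated for deviations. It should be made before outcome data are examined; Appendix B lists the trial as recruiting. The downside is that a result between the two levels cannot be claimed as significant under the flat 0.0125 rule; Holm recovers part of that. On the plan's own effect size and 180 completers, power for a single outcome at 0.0125 remains about 0.86 to 0.97 for the two values of ε tried.
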